#### Secondary endpoints

2.4.2

Secondary endpoints are a measurement of DBS efficacy and acceptability.

##### DBS efficacy

2.4.2.1

For the measurement of DBS efficacy, we rely on:

Duration of hospital stays in a specialized center. Comparison between the two years before inclusion in the STIMARS protocol and the two years after inclusion (with a 6-month washout interval right after the DBS surgery to consider stimulation start and initial parameter adjustments).BMI monitoring in a standardized way. Monthly measurements during the follow-up according to the calculation rule: weight (kilograms)/height² (square meter) during each follow-up visit with the referring physician. Comparison between the two years before inclusion and the two years after inclusion (with a 6-month interval to consider stimulation start and first parameter adjustments). Additionally, body composition will be assessed by multifrequency impedancemetry Z-Métrix^®^ (Bioparhom). Resting energy expenditure will be measured by indirect calorimetry with Omnia 1.6.10 - Quark RMR (COSMED).Changes in preoperative and postoperative scores on the various clinical dimensions of AN via various questionnaires (see **Table 3**). Eleven dimensions of eating disorders will be measured by the *Eating Disorder Inventory-2* (EDI-2) (47). Levels of anxiety and depression will be assessed through the *Hospital Anxiety and Depression* Scale (48). The presence and severity of obsessive-compulsive disorder will be measured through the *Yale-Brown Obsessive Compulsive Scale* (Y-BOCS) (49, 50). These data will be collected during the preoperative, early postoperative, and late postoperative neuropsychological assessments (3 months, 12 months, and 23 months after inclusion, respectively). Additionally, the Zarit scale aims to evaluate the burden of the patient’s severe and resistant anorexia nervosa on a caregiver: the caregiver present at the inclusion visit must be 1) present during the patient’s neuropsychological assessments or 2) available by telephone to complete the scale (duration of the interview: 15 minutes, including 5 minutes for completing the scale).Changes in neurocognitive dimensions. All cognitive tasks will be performed on computers (with MATLAB^®^) under the supervision of a trained neuropsychologist.Changes in pupillometry assessments (**Figure 1**). Pupillometry measures the pupil diameter for an objective evaluation of the emotional impact of a task on the subject. The pupil dilates in response to positive and negative emotions, as well as in response to light. Using a subtractive method, the effect of light is removed and the emotional impact is quantified. We use pupillometry (dedicated eye tracker, chin rest, and a dedicated computer; see **Figure 1**) to comparatively assess the emotional impact caused by 60 computer-viewed pictures belonging to different types of stimuli: 12 neutral images (e.g. image of a book), 12 negative images (e.g. a violent image), 12 pleasant images (e.g. image of babies, kittens), 6 images of caloric foods (e.g. image of ice cream), 6 images of lean food (e.g. image of carrots), and 12 images of standardized silhouettes depicting different BMI. Emotional stimuli (neutral, pleasant, and negative images) were taken from the International Affective Picture System (IAPS) (51). Food pictures come from the Open Library of Affective Foods (52). Standardized silhouettes were computer-generated pictures (53), representing a naked woman (height 165 cm) varying in BMI, with underweight silhouettes (BMI: 12–16 kg/m2), normal weight silhouettes (BMI: 19–23 kg/m2) and overweight silhouettes (BMI: 26–30 kg/m2). All pictures are in grey levels, 8 bits, 1024x768px, modified with TheGIMP^©^. The task was programmed using MATLAB^®^. Stimuli were randomized into 12 blocks. Each block containing five pictures: three IAPS pictures (one positive, one negative, one neutral), one food picture, and one standardized silhouette. Each picture will be shown for 6s with a 2s in‐between fixation point. The quantitative aspect of the emotional impact is given by the changes in pupil diameter, unlike the sign of the emotion (positive or negative) which requires an additional questionnaire: at the end of the task, subjects will view the pictures a second time and will be asked to evaluate valence and emotional arousal, using a simple numeric scale. Questions will be ‘Would you rate this image as pleasant or unpleasant?’ from 1 (very unpleasant) to 9 (very pleasant), and ‘What is the emotional impact, how powerful is the feeling caused by this picture?’ from 1 (very low) to 9 (very high).Time specificities (capacity to delay reward) will be measured through the Delay Discounting Task (DDT). In the DDT, subjects are presented with two options of various amounts of money available at different delays: one smaller amount of money but available within a shorter delay (“Smaller Sooner”, SS) and one larger amount of money but available in a longer delay (“Larger Later”, LL). This task allows measuring the subjective value that a person perceives in a given reward depending on the delay.Cognitive flexibility will be measured through the Brixton test (54, 55), the Trail-Making Test (56) and the Wisconsin Card Sorting Test (57). Previous research suggests that this test has no practice effect (58).The Slip-of-action Task (SOAT) (59, 60) will assess reward-motivated versus habit-driven behavioral choices. The task is detailed in a previous publication (18) and measures the tendency to lose sight of a goal (goal/reward-motivated choices) due to the activation of habitual responses (habit-driven choices).

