**Methods and analysis:**

This is a prospective, multicentre, single-arm, open-label, non-randomized pilot trial of bilateral nucleus accumbens deep brain stimulation for severe and enduring AN. Patients will be followed up for 24 months after deep brain stimulation. The main objective of this study is to measure the safety and feasibility of nucleus accumbens deep brain stimulation in this population. The recruitment rate will be collected prospectively. Potential deep brain stimulation efficacy will be monitored by changes in: 1) health-related quality of life; 2) weight; 3) eating disorder symptomatology; 4) neuropsychological changes of cognitive flexibility, habits formation, emotional processing and central coherence; 5) psychiatric comorbidities (anxiety, depression, obsession). Local field potential recordings during an exposure task will be proposed to the patients. Additionally, caregiver quality of life will be assessed.

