### Background and rationale

1.1

Anorexia nervosa (AN) is the psychiatric disorder with the highest mortality rate – the standardized mortality rate is higher than four – due to somatic complications and suicide (1–3). The median age at onset of AN is 15.5 years old (4). Despite the lack of longitudinal data and significant heterogeneity of care pathways, approximately 20% of patients develop a long-lasting disorder (5). In a staging approach, this subgroup of patients is considered to suffer from “severe and enduring AN” (SE-AN). Patients with SE-AN may benefit from specific treatments focusing on improving their social functioning and quality of life (6). At present, treatments for SE-AN are largely lacking (7).

The core position of the nucleus accumbens (NAc) is now well described in AN (8). NAc is involved in top-down control in decision-making through a fronto-accumbal hyperconnectivity (9), in food choice (10), and in body image disturbance through its connectivity with the insula (11). Numerous studies identified the mesocortico-limbic dopaminergic system in controlling eating behavior and body weight (12–15). Projections from the ventral tegmental area to the NAc are largely involved in the motivational aspect of food intake (16). Functional neuroimaging studies performed on acute and weight-recovered patients show that the NAc is a key structure associated with remission after refeeding (9, 17). The specific faculty to delay reward, as measured by the delay discounting task, involves the NAc (17). Preclinical studies identified an imbalance between ventral (NAc) and dorsal (caudate/putamen) striatum for the transition from reward-guided and goal-directed behaviors to automatic habitual behavior (18). These compulsive behaviors are common to both AN and obsessive-compulsive disorder (19).

Deep brain stimulation (DBS) of the NAc in mouse models of AN shows increase of food intake (20, 21) while, in a domestic pig model, DBS of the NAc shows modulation of the activity of the reward circuit structures (22). Recent series have reported promising results with NAc deep brain stimulation in patients suffering from severe and enduring AN (23–25).

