#### Primary endpoint

2.4.1

The primary endpoint is the proportion of serious adverse reactions (SAR) occurring in the patients included in the study. For continuous safety monitoring, we adopt a binomial sequential test, re-evaluated with each new patient, with the following parameters: maximum proportion of patients with SAR 15%, bilateral alpha 15%, beta 20%. The maximum and minimum tolerance limits for SAR were determined using the toxbdry function of the clinfun package version 1.0.15 of R. Taking the lower limit as a precaution, **Table 2** summarizes the maximum number of patients with a tolerable SAR to respect a threshold below 15%. This study design is justified because complications directly related to surgery typically appear within the first month (43). There are long-term complications of DBS which are taken into account in the protocol as the patients are followed up (44). These long-term complications must be put into perspective with the risk of death associated with SE-AN (2). The first three patients will be included sequentially with an interval of at least one month to ensure that there are no systematic adverse effects. If the 15% threshold of SAR in the study population is exceeded, as assessed in a sequential procedure, the study will be stopped.

**Table 2 T2:** Maximum number of patients with a serious adverse event to respect a threshold below 15%.

Number of included patients	Maximum limit of the interval
3	1
4	1
5	1
6	1
7	1
8	2
9	2
10	2
11	2
12	3

Highlighted numbers correspond to the maximum tolerated threshold of patient(s) presenting a serious adverse reaction related to the surgery (rounded down).

Serious adverse events are defined by the French National Agency for the Safety of Medicines and Health Products (ANSM) based on the French Public Health Code: “A serious adverse event is an adverse event that is lethal, or likely to be life-threatening, or leading to significant or lasting disability or incapacity, or causing or prolonging hospitalization, or manifesting itself as a congenital anomaly or malformation.”

SAR are serious adverse events directly caused by the intervention. In particular, we look for:

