Patients are informed by their referring practitioner of the existence of the protocol and the surgical possibilities before the selection visit (so outside the trial itself). Patients eligible for inclusion are discussed at a multidisciplinary meeting attended by psychiatrists, psychologists, neurologists, neuroradiologists, and neurosurgeons. Referring practitioners work in reference centers for the management of anorexia nervosa: patients deemed clinically or psychologically unstable are not presented at the multidisciplinary consultation meeting. Only after a positive collegial opinion has been obtained from the multidisciplinary consultation meeting can patients undergo the inclusion visit.

Patients who meet the inclusion criteria and do not have exclusion criteria are informed about the protocol during the selection visit. The inclusion visit takes place at least 2 weeks after the protocol description: this is a mixed consultation necessarily associating a psychiatrist specialized in the management of eating disorders and a neurosurgeon specialized in DBS. The patient’s trusted person and/or his relatives is present during this consultation. During the inclusion visit, the patient is asked to give or not his consent to participate in the study. The necessary steps before a DBS surgery (anesthesia assessment, MRI, blood tests) and the first neurocognitive assessment are performed during the preoperative visit. The patient has at least three visits and 8 weeks between the selection visit and the surgery.

The duration of follow-up after patient inclusion is 24 months. The patient is followed up at least monthly by the referring physician. These visits are part of the patient’s routine care: their frequency can therefore be modulated according to the care required but can never be less than monthly. The minimal investigations conducted during these consultations are as follows: 1) structured psychiatric interview; 2) measurement of BMI; 3) collection of SAR; 4) verification of the functioning (impedance measurement in particular) of the neurostimulation using the appropriate equipment (Physician programming system, Apple™ Ipad Mini, ABBOTT).

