## Discussion

3

Patients suffering from treatment-resistant AN have limited treatment options nowadays. They exhibit poor outcomes, even in expert centers (71). Our study protocol aims to support the growing literature on DBS for treatment-resistant AN.

Costs associated with AN are mostly related to hospital stays (72). The average length of stay for patients with AN is higher than 100 days in Europe (73). During hospitalization in expert centers, refeeding approaches lead to a clinical remission according to the BMI, even with higher-calory refeeding (74). However, relapse of AN arises frequently during the 18 months after hospitalization (75). This underlines the need to manage more community-oriented therapeutic approaches in AN patients. Our study does not require very low BMI to include the patient: the aim is more to manage the deinstitutionalization of AN patients than to obtain weight gain.

Whereas the safety of DBS is now well-established in neurological conditions, this question remains for treatment-resistant AN patients (76, 77). This study will help to refine the expected complication rate in front of these malnourished patients. Moreover, DBS is reversible and customizable. These two points explain why DBS, a reversible neuromodulation technique, should always be considered rather than irreversible lesion techniques (such as thermolesions, radiosurgery) in psychiatric patients.

The main limitations of this study are the single arm and open-label characteristics. This study design has been considered as mandatory by the French authorities. After confirmation of the DBS safety in patients with treatment-resistant AN, a larger study will be possible. The small study sample is in line with the main outcome of safety. We have decided to monitor the patient’s quality of life with two scales translated and validated in French, to minimize the common misgrading of quality of life in anorexia nervosa patients (78). However, these scales are generic and an eating disorder-specific measure would represent a nice to further studies (79). The measurement of healthcare intervention acceptability should investigate multiple aspects: despite numerous psychiatric follow-up visits, only limited data will be collected during the protocol (62). The development of a specific theory-informed questionnaire about DBS for SE-AN would have been a significant improvement and should be done for the next studies (80, 81).

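### Hospital stay is compared as a total duration with no time denominator, and the washout shortens only the after window, so totals taken as written favour DBS by about 25% to 32% with no effect and no losses

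*Protocol article*

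**What the plan says.** Section 2.4.2.1 (DBS efficacy) of the protocol article lists first "Duration of hospital stays in a specialized center". The contrast is "Comparison between the two years before inclusion in the STIMARS protocol and the two years after inclusion". A stretch is then cut out on the after side only, in these words: "with a 6-month washout interval right after the DBS surgery to consider stimulation start and initial parameter adjustments". No rate, denominator or matching gap on the before side is given.

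The end of the after window is not settled. The abstract says "Patients will be followed up for 24 months after deep brain stimulation", and Table 4 places the last trial visit 24 months after surgery. Section 2.5 (Participant timeline) says "The duration of follow-up after patient inclusion is 24 months".

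Section 2.8.2 (Statistical analysis) compares quantitative data by paired t-test, repeated-measures ANOVA or paired Wilcoxon at a two-sided 5% level. On incomplete data it says only that the extent of missingness will be reported. The sample size is 12 (section 2.8.1).

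The Discussion gives this endpoint its weight: "the aim is more to manage the deinstitutionalization of AN patients than to obtain weight gain".

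**The concern.** A total of days grows with the time over which it is counted. Here the before window is a full two years for everyone, because each patient has lived through it by the time of inclusion. The after window loses six months to the washout, and in some patients it may lose more to death or withdrawal. Section 1.1 describes a disorder in which "the standardized mortality rate is higher than four", and section 2.4.2.1.1 counts study completion as an outcome, so shortened follow-up is foreseen.

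A paired test on totals would therefore show fewer hospital days after surgery when nothing has changed. There is no control arm to reveal this. The abstract says that the trial will supply an effect size for larger studies, so the bias could be carried into their planning.

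**Working it through.** The protocol gives no expected hospital days, standard deviation or effect size for this endpoint, so there is no figure of its own to reproduce. The checks below ask what totals would show if DBS had no effect.

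**1. Window lengths with everyone complete** (constant monthly rate of hospital days)
- Before: 24 months.
- After, with follow-up to 24 months after surgery: 24 − 6 = 18 months. Ratio 18/24 = 0.75, a fall of 25%.
- After, with follow-up to 24 months from inclusion: surgery is taken as about 7 weeks after inclusion (assumed from Table 4, read as 3 weeks plus 4 weeks), or 49/30.4375 = 1.6 months. If those weeks are not counted as after, 24 − 1.6 − 6 = 16.4 months. Ratio 16.4/24 = 0.68, a fall of about 32%. If they are counted, the window is again 18 months.
- If two full years are meant to start after the washout, the windows are equal, but the second ends 6 + 24 = 30 months after surgery, beyond the 24-month follow-up.

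**2. Further shortening by loss** (18-month window, 12 patients, days totalled as observed)

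Mean after time = [(12 − k) × 18 + k × (t − 6)] / 12, with k patients lost at month t after surgery.
- k = 1, t = 12: (11 × 18 + 6)/12 = 17.0 months; 17.0/18 is a fall of 5.6%.
- k = 1, t = 9: (198 + 3)/12 = 16.75, a fall of 6.9%.
- k = 1, t = 18: (198 + 12)/12 = 17.5, a fall of 2.8%.
- k = 2, t = 12: (180 + 12)/12 = 16.0, a fall of 11.1%.
- k = 3, t = 12: (162 + 18)/12 = 15.0, a fall of 16.7%.

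These come on top of the 25%. The limit for one patient is zero days over the whole after window: 1/12 = 8.3%.

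The protocol gives no absolute risk of loss. At assumed two-year risks of death or withdrawal of 5%, 10% and 20%, the chance of at least one among 12 is 1 − 0.95^12 = 46%, 1 − 0.90^12 = 72% and 1 − 0.80^12 = 93%.

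**3. Effect on the paired t-test** (simulation, n = 12, two-sided 5%, 40,000 runs, no DBS effect)

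Assumptions: 100 hospital days per 24 months, gamma rates with coefficient of variation 0.5 between and 0.5 within patients, and loss time uniform over the after window. The table gives the chance of a significant result in favour of DBS; about 2.5% is nominal.

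| Scoring | 0 lost | 1 lost | 2 lost | 3 lost |
|---|---|---|---|---|
| Totals, 24 vs 18 months | 19.5% | 23.4% | 28.1% | 33.1% |
| Lost patients left out, 24 vs 18 months | about 20% | 17.4% | 15.6% | 13.8% |
| Totals, 24 vs 24 months | 2.1% | 2.9% | 4.5% | 6.3% |
| Days per month observed | about 2% | about 2% | about 2% | about 2% |

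The unequal window does most of the damage, and losses add to it only if truncated totals are used. The last row assumes that loss is unrelated to the admission rate.

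**4. What a rate does not settle**

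A patient who dies without an admission after the washout has a rate of 0, the best possible value. Counting days alive and out of hospital reverses the lean. On 100 hospital days in 730, the before value is 630. One death at the start of the after window gives 0 and moves the mean by 630/12 = 52.5 days against DBS.

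**The case against.** The best defence is that the article does not say how an incomplete after window is scored. Such a rule commonly belongs in the analysis plan, which is not shown. That is fair, and it limits what can be said about losses.

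A reader might infer that every death or withdrawal is scored as fewer hospital days and so always counts for DBS. The documents do not support this:
- No scoring rule is stated, and leaving the patient out of the pairing fits the text equally well. In that case losses do not add to the bias.
- Withdrawal from the study need not end the record of admissions; the article does not say.
- A patient who deteriorates may spend much time in hospital before dying and exceed the before total.
- The 8.3% shift needs a patient with no hospital days in the whole after window.

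It can also be said that this is a secondary measure in a pilot that section 2.8.1 describes as not meant to assess effectiveness, and that deaths would be visible through safety reporting. Both are true and keep the point modest.

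Neither answers the window problem. The endpoint as a duration, the calendar windows and the one-sided washout are all written into section 2.4.2.1, and the paired tests in section 2.8.2 do not correct for unequal time.

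**Conclusion.** The point holds as a conditional one. If hospital days are totalled over the windows as written, the comparison favours DBS by about 25% with no effect and no losses. The figure is about 32% if follow-up ends 24 months after inclusion, surgery comes about 7 weeks after inclusion and those weeks are left out. Both figures rest on a constant admission rate.

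Losses are the smaller part and depend on scoring. Under truncated totals, one of 12 patients lost at month 12 after surgery takes a further 5.6% off the after mean (2.8% to 6.9% for months 18 to 9), usually but not always in favour of DBS. Death is the firmer case; withdrawal matters only if admissions are then no longer collected.

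This should be corrected because the measure is the one closest to the trial's stated aim. It does not touch the primary safety endpoint.

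**What to change.** In section 2.4.2.1, or in the analysis plan:
- Compare windows of equal length before and after, with start and end dates fixed in advance, or express hospital days per month alive and observed in each window. Equal windows remove the washout imbalance; the rate also removes the effect of shortened follow-up.
- State whether the after window ends 24 months after inclusion or after surgery, and whether the weeks between inclusion and surgery are counted.
- State whether admissions continue to be collected after withdrawal.
- Report the numbers and dates of deaths and withdrawals beside the comparison, because a rate still scores a patient who dies unadmitted as 0.
- Add days alive and out of hospital as a sensitivity analysis. Note that nobody could die in the before window, so this version leans against DBS. It should not replace the main measure.

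The cost is analysis wording only. The endpoint already needs the hospital-stay data, and deaths are reported as serious adverse events. The reported reduction in hospital days may be less favourable.

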### Participant timeline

2.5

A detailed schedule for trial participants is presented in **Table 4**.

**Table 4 T4:** Detailed schedule for trial participants.

Assessment	*Visit(s) with the referring physician* (prior to the trial)	Eligibility Visit 1 -4 weeks	Enrollment Visit 2 Week 0	Preoperative Visit 3 weeks after Visit 2	Surgery 4 weeks after Visit 3	Postoperative Visits 5-29					End of trial Visit 30 24 months after surgery (+/- 1 week)	*Post-trial* At least every 3 months
						Every month (+/- 1 week)	Every 2 months (+/- 1 week)	3 months after surgery (+/- 1 week)	12 months after surgery (+/- 1 week)	23 months after surgery (+/- 1 week)		
Eligibility screen	**X**	**X**										
Informed consent for trial			**X**									
Care-taker informed consent for trial			**X**									
Informed surgical consent				**X**								
Neurosurgical examination			**X**	**X**	**X**		**X**					**X**
Psychiatric examination		**X**	**X**		**X**	**X**						**X**
Body Mass Index measurement		**X**	**X**	**X**	**X**	**X**	**X**	**X**	**X**	**X**	**X**	**X**
Serious Adverse Events monitoring				**X**	**X**	**X**	**X**	**X**	**X**	**X**	**X**	**X**
Anesthetic evaluation				**X**								
Biological tests				**X**	**X**							
MRI				**X**								
Deep brain stimulation surgery					**X**							
Postoperative CT					**X**							
The Eating Disorder Inventory 2				**X**				**X**	**X**	**X**		
Psychiatric Scales												
1. Hospital Anxiety and Depression Scale 2. Yale Brown Obsessive-Compulsive Scale 3. Scale for Suicide Ideation				**X**				**X**	**X**	**X**		
Neurocognitive Scales												
1. Montreal Cognitive Assessment 2. Delay Discounting Task 3. Wisconsin Card Ranking Test 4. Brixton Test 5. Trail Making Test A and B 6. Slip-of-action test 7. Habits vs Goal Directed Behavior test 8. Dubois Five Word Test 9. Rey/Taylor Figure				**X**				**X**	**X**	**X**		
Quality of life Scales												
1. SF-36 Quality of Life Questionnaire 2. Global Assessment of Functioning Scale				**X**				**X**	**X**	**X**		
Care-taker Scale												
1. Zarit Burden Inventory (to be completed by the care-taker)				**X**				**X**	**X**	**X**		
Pupillometry				**X**				**X**	**X**	**X**		

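### Hospital days are compared over 24 months before inclusion and at most 18 months after surgery, so totals would fall by about 25% with no effect of stimulation

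*Protocol article*

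**What the plan says.** Section 2.4.2.1 (DBS efficacy) lists first among its efficacy measures "Duration of hospital stays in a specialized center". The periods to be compared are stated as "the two years before inclusion in the STIMARS protocol and the two years after inclusion (with a 6-month washout interval right after". That interval starts at surgery and is meant to cover the beginning of stimulation and its early tuning. The section gives no rate per unit of time and no matching cut to the period before inclusion. Section 2.8.2 adds only general paired tests at a two-sided 5% level.

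The end of follow-up is anchored in two ways. The abstract and Table 4 place it 24 months after surgery. The text of Section 2.5 places it 24 months after inclusion. Section 2.4.2.1 also dates the neuropsychological assessments from inclusion, whereas Section 2.5 and Table 4 date the postoperative ones from surgery.

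For the gap between inclusion and surgery, Table 4 prints "Preoperative Visit 3 weeks after Visit 2" and "Surgery 4 weeks after Visit 3". Section 2.5 requires at least 8 weeks between the selection visit and surgery.

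The Discussion links hospital time to the purpose of the trial: "the aim is more to manage the deinstitutionalization of AN patients than to obtain weight gain".

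**The concern.** Days in hospital accumulate with calendar time. If one window is shorter, its expected total is lower even when the patient's rate of hospitalisation has not changed. Here the shorter window is always the one under stimulation, so the distortion runs in one direction, towards benefit.

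The trial has a single arm, so no comparator would show the same artificial fall. The endpoint is secondary, but it is the efficacy measure closest to the deinstitutionalisation aim in the Discussion. The article also says that the trial should supply an effect size for a larger study. It does not say on which outcome. If hospital days were used, the planning value would contain a reduction that comes from the window lengths alone.

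**Working it through.** The plan gives no expected effect or power for this endpoint, so there is no figure of its own to reproduce. The check is arithmetic on the stated windows.

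**Inputs**
- Period before: 24 months before inclusion (Section 2.4.2.1).
- Washout: 6 months from surgery, removed from the later period only (Section 2.4.2.1).
- End of the later period: 24 months after surgery (abstract, Table 4) or 24 months after inclusion (Section 2.4.2.1 as worded, Section 2.5 text).
- Inclusion to surgery, upper value: 3 + 4 = 7 weeks from Table 4 as printed. The 3 may be a visit number rather than a number of weeks, so this value is uncertain.
- Inclusion to surgery, lower value: 8 − 4 = 4 weeks, from the 8-week minimum in Section 2.5 less the 4 weeks between eligibility and enrolment in Table 4.
- Conversion: 4.348 weeks per month, so 4 weeks = 0.92 months and 7 weeks = 1.61 months.

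**Formula**

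With a constant rate of hospital days and no effect of stimulation, apparent reduction in total days = 1 − (months counted after) / 24.

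**Results**

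| End of window | Months counted after surgery | Ratio to 24 | Apparent reduction |
|---|---|---|---|
| 24 months after surgery | 24 − 6 = 18.0 | 0.750 | 25.0% |
| 24 months after inclusion, 4-week gap | 24 − 0.92 − 6 = 17.08 | 0.712 | 28.8% |
| 24 months after inclusion, 7-week gap | 24 − 1.61 − 6 = 16.39 | 0.683 | 31.7% |

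If the window ends 24 months after inclusion but the untreated weeks before surgery are kept in it, 24 − 6 = 18 months count and the result is again 25.0%. Those weeks would then be credited to the stimulation period. The text does not say where they belong.

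As an example, take an assumed constant 100 hospital days per year. A patient has 200 days before inclusion. The later window then holds 150 days (18.0 months), 142 days (17.08 months) or 137 days (16.39 months), with nothing changed.

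**Could the later period be a full 24 months?** Only if it started after the washout, which needs 24 + 6 = 30 months from surgery. Table 4 ends the trial at 24 months.

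**After correction.** Dividing days by months observed in each window, or cutting the earlier window to the same length as the later one, gives an expected change of 0% under no effect.

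**The case against.** The strongest objection is that the section never says total days. Mean length per stay would not shrink mechanically with a shorter window, and the Discussion itself mentions average length of stay. Scaling by observed time is also a detail that a full protocol or analysis plan might supply. This stands as a condition: the 25% applies to cumulative days compared as totals. It does not remove the point. The section fixes two calendar periods of unequal countable length, and total time in hospital is the natural reading for an aim of deinstitutionalisation.

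Some stronger readings are tempting but not supported:
- **A reduction of 32% as the main figure.** It needs both the inclusion anchor and the uncertain 7-week gap. The 25% needs neither.
- **A specific false-positive rate.** The article gives no hospital-day rates, so any such rate rests on assumptions. In an illustrative simulation (12 patients, paired t-test, 3 to 8 hospital days per month, between-patient coefficient of variation 0.6, 18-month window), a false significant reduction occurs in about 7% to 14% of trials with 40-day mean stays. With 100-day stays, nearer to the average of over 100 days cited in the Discussion, it is about 4% to 7%. Nominal is 2.5% in that direction. The bias in the estimate does not depend on these inputs.
- **The same bias in BMI.** The BMI item has a similar rule ("Comparison between the two years before inclusion and the two years after inclusion (with a 6-month interval"), but BMI is a level measured monthly, and fewer months do not lower it mechanically.
- **A threat to the trial's main conclusion.** The primary endpoint is serious adverse reactions, and Section 2.8.1 says that the pilot is not meant to evaluate effectiveness.

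**Conclusion.** The point holds for cumulative hospital days. As written, at most 18 months after surgery are compared with 24 months before inclusion, which builds in an apparent reduction of about 25% when stimulation does nothing. If the window closes 24 months after inclusion, the built-in reduction is about 29% to 32%, depending on an assumed 4- to 7-week gap to surgery.

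This rests on two assumptions: that duration means total days, and that the underlying rate is constant. Regression to the mean is a separate matter and is not counted here. The artefact disappears if days are expressed per unit of time or the windows are matched, but the article states neither. Because the endpoint is secondary and the trial is a pilot, this is a should-fix.

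**What to change.** 1. Define the endpoint in Section 2.4.2.1 as hospital days per month of observed time in each window. Alternatively, use equal 18-month windows: the 18 months before inclusion against months 6 to 24 after surgery.
2. State that patients who die or leave contribute only the time for which they were observed.
3. Use one anchor, inclusion or surgery, consistently in the abstract, Section 2.4.2.1, Section 2.5 and Table 4, and state where the weeks between inclusion and surgery fall.

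The cost is a wording change and a division by time, with no added visits. It does require admission and discharge dates for both windows. The article does not list these among the scheduled items, so their collection should be confirmed. The apparent benefit will be smaller than under the current wording.
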